### Clinical implications

In the Netherlands, GPs are the ‘gatekeeper’ to the hospital. Therefore, a clinical decision rule for acute chest pain is probably most beneficial in primary care. Based on previous literature, the clinical decision rule presented in this study may decrease hospital referrals of patients with acute chest pain by 10%.^45 46^ Thereby, this strategy may reduce uncertainty for patients and doctors, increase patient satisfaction, decrease (unnecessary) diagnostic tests and relieve pressure on healthcare personnel and the healthcare system. Furthermore, it may lead to a substantial reduction in societal costs as was shown in a previous observational Norwegian study.^17^ In the Netherlands, a patient referred to the hospital for acute chest pain on average costs €1580, whereas a primary care consultation plus hs-cTnI-POCT measurement is estimated to cost on average €73.^13 38^ Therefore, if the decision rule would be implemented in 50% of general practices and assuming a 10% reduction in referrals, this could potentially lead to an estimated cost reduction of €31 million in The Netherlands each year.^49^

### Generalisability

The current RCT will compare the clinical decision rule to regular care in general practices in three regions in The Netherlands, including urban and rural areas. After careful instruction on the inclusion criteria, the GPs in these practices will decide on the eligibility of individual patients. Although differences among GPs (eg, a less experienced GP may include different patients than an experienced GP) may lead to inclusion bias, this situation resembles daily clinical practice. Hence, the results of this study will be generalisable to the rest of The Netherlands and other countries with a similar primary care system, where the GP functions as a gatekeeper (eg, the UK, Scandinavian countries and Canada). In addition, we will measure the GP’s working experience, which enables us to quantify this potential bias.

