## Methods and analysis

### Study design

The POB HELP study is a clustered diagnostic RCT. The study will be conducted in general practices in three regions in the Netherlands (Leiden, Maastricht and Venlo). General practices will be randomised to the intervention or control group in a 2:1 ratio. Randomisation is stratified for the three regions to ensure even distribution of rural and urban areas. Randomisation is done by Castor Electronic Data Capture using a variable block randomisation method.^18^ Patient inclusion started on 18 August 2021 and the study is planned to end on 1 July 2024.

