### Study population

Patients visiting their GP, or visited by their GP, for acute chest pain symptoms in which the GP suspects an ACS, are eligible for inclusion. Patients who contact their GP by telephone with acute chest pain highly suspicious for ACS are not eligible for inclusion. For these patients, an ambulance is sent directly to the home address by the doctor’s assistant, in accordance with usual care. Exclusion criteria are: age <18 years, trauma preceding the pain, inability to speak Dutch or understand the informed consent form, onset of chest pain within less than 1 hour and haemodynamic instability (table 1). Patients who match the eligibility criteria and provide informed consent are included in the study.

**Table 1 T1:** Inclusion and exclusion criteria

Inclusion	Exclusion
≥18 years of age	<1 hour since onset of symptoms
Acute chest pain	Inability to speak or understand Dutch
Seen by the general practitioner	Haemodynamic instability
	Trauma preceding chest pain

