### Intervention

For patients included in general practices randomised to the intervention group, the GP will apply a clinical decision rule consisting of the Marburg Heart Score (MHS) and a hs-cTnI-POCT (figure 1).^3 20 21^

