### Final diagnosis

The final diagnosis will be made based on GP’s medical records, including all letters from hospitals. All cases will be reviewed by an independent endpoint committee consisting of a cardiologist and GP for adjudication of the final diagnosis and the occurrence of MACE. The committee will be blinded for the randomisation and hs-cTnI on presentation. In case of disagreement, a second cardiologist will be consulted. The final diagnosis will be classified as ACS, stable coronary artery disease, cardiac but non-coronary disease, non-cardiac chest pain or death. ACS comprises myocardial infarction (ST-segment elevation myocardial infarction (STEMI) and non-STEMI (NSTEMI)) and unstable angina pectoris. Myocardial infarction is defined conform the fourth universal definition of myocardial infarction.^33^

A coronary angiogram (CAG) is the golden standard to establish the presence of coronary artery disease. However, CAG is costly and not without risk (eg, bleeding in approximately 7% and procedure-related myocardial infarction in approximately 6% of patients undergoing CAG).^34 35^ Therefore, we consider it too invasive and essentially unethical to perform a CAG in each patient in this relatively low-risk population. Hence, we will use a delayed reference standard, defined as ACS and MACE at the index consultation, within 6 weeks and 6 months after inclusion, to determine the diagnostic accuracy of the decision rule. The delayed reference method has been reported as a valid alternative if a golden standard test is too invasive and the disease is not self-limiting.^36^ This method has been used in similar studies before.^7 20 32 37^

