The cost-effectiveness of the clinical decision rule will be assessed alongside the trial. The analysis will be performed from a societal perspective. The costs are divided into healthcare costs and non-healthcare costs. Healthcare costs include those of the intervention and other healthcare use during follow-up. The costs of the clinical decision rule will be based on microcosting including the duration of the GP consultation, medical equipment and materials used. Healthcare use will be assessed by questionnaires at 6 weeks and 6 months follow-up. In this questionnaires, patients will be asked to fill out their total healthcare utilisation, such as GP visits, outpatient clinic visits, ED visits and hospital admissions for any reason. Reference prices published in the Dutch costing manual will be used to value healthcare use.^38^ To calculate non-healthcare costs, patients will be asked to note absence from paid and unpaid work. Productivity costs will be calculated using the friction cost method. Quality-adjusted life years (QALYs) will be calculated from utility scores from the EQ-5D-5L questionnaire administered at baseline, 6 weeks and 6 months follow-up.^39 40^ Finally, costs and QALYs between the control and intervention groups will be compared.

To assess the GP’s adherence to the recommendations of the decision rule, the outcome of the decision rule will be compared with the GP’s policy as reported by the GP. To assess the effect of the clinical decision rule on patients’ reassurance, patients will be asked to fill out the State-Trait Anxiety Inventory after the index consultation.^41^ To evaluate the diagnostic accuracy of the GP’s gut feeling, GPs will be asked to estimate the likelihood of ACS using the gut feeling questionnaire directly after the index consultation.^42 43^ The outcome of this questionnaire will be compared with the occurrence of MACE within 6 weeks. In all patients with an ECG, the HEART score will be scored retrospectively based on the information on the inclusion form filled out by the GP. The outcome will be compared with the occurrence of MACE within 6 weeks.^31^

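### GPs who know their practice's arm decide whom to include, so referral rates may compare different case mixes; recording GP experience does not measure this and the described comparison names no adjustment

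*Protocol article*

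**What the plan says.** Under Study design: "General practices will be randomised to the intervention or control group in a 2:1 ratio". Region is the only stratification factor.

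The text of Study population makes entry depend on the GP's judgement: patients seen "for acute chest pain symptoms in which the GP suspects an ACS, are eligible for inclusion". Table 1 in the same section lists acute chest pain and does not mention suspicion of ACS. Generalisability confirms who decides: "After careful instruction on the inclusion criteria, the GPs in these practices will decide on the eligibility of individual patients".

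Under Intervention: "For patients included in general practices randomised to the intervention group, the GP will apply a clinical decision rule". Staff, including at least one GP per practice, are trained on the analyser before the study starts. The only blinding described, under Final diagnosis, is that of the endpoint committee: "The committee will be blinded for the randomisation and hs-cTnI on presentation".

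Inclusion bias is acknowledged in the strengths and limitations list and again under Generalisability. There it is put down to differences among GPs, with more and less experienced GPs as the example. Working experience will be recorded, "which enables us to quantify this potential bias".

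Under Statistical analysis, referrals are compared as percentages with a χ² or Fisher test, with generalised estimating equations (GEE) for correlation within practices. Baseline characteristics are compared between groups. No covariate is named for the referral comparison.

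**The concern.** In a cluster trial, randomisation balances practices. It balances patients only if recruitment works the same way in both arms. Here the entry criterion is a subjective threshold, applied by someone who knows the arm. A GP with a quick finger-stick test has a reason to include patients of lower suspicion, and the article itself suggests that the rule may help with atypical presentations. A control GP has no such reason. The difference in wording between Table 1 and the text leaves the threshold less firmly fixed than it should be.

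The first primary endpoint is a proportion whose denominator is the set of patients the GPs chose to include. Extra low-risk patients in the intervention arm lower its referral rate even if the rule changes no decision.

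GP experience does not help with this. It is a property of the GP that randomising practices tends to balance, and it does not show whether GPs with the device enrol different patients from GPs without it. GEE corrects the variance and not this bias. Intention-to-treat begins at inclusion, after selection has acted.

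**Working it through.** **Inputs from the article (Sample size calculation):** control referral 40%, intervention 30%, two-sided alpha 0.05, power 80%, intraclass correlation (ICC) 0.05, 448 control and 896 intervention patients before loss to follow-up. Average cluster size is not given.

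**Inputs that are assumptions:** the rule has no effect; intervention practices enrol a fraction *e* = 10–20% of extra patients on top of those they would otherwise include; these are referred at rate *r* = 5–10%. Nothing in the article supports these values. They only show the scale.

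**Design effect implied by the plan.** For 40% versus 30% at 1:2, an individually randomised trial needs 265 controls (pooled variance) or 271 (unpooled). The stated 448 implies 448/265 = 1.69 or 448/271 = 1.65. At ICC 0.05 that is 1 + 0.69/0.05 ≈ 14.8 or 1 + 0.65/0.05 ≈ 14 patients per practice. An assumed 15 per practice gives 265 × 1.70 = 451, close to 448. The stated size is therefore consistent with its inputs, but without the cluster size it cannot be confirmed. I use 1.65–1.69 as an assumed design effect.

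**Spurious fall in the referral rate.** Observed intervention rate = (0.40 + *e* × *r*) / (1 + *e*).

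- *e* = 0.10, *r* = 0.10: 0.410/1.10 = 0.373, a fall of 2.7 points
- *e* = 0.10, *r* = 0.05: 0.405/1.10 = 0.368, a fall of 3.2 points
- *e* = 0.20, *r* = 0.10: 0.420/1.20 = 0.350, a fall of 5.0 points
- *e* = 0.20, *r* = 0.05: 0.410/1.20 = 0.342, a fall of 5.8 points

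**Chance of a significant result with no true effect.** With design effect 1.65 the effective sizes are 448/1.65 = 271.5 and 896/1.65 = 543.0. The standard error is √(0.40 × 0.60/271.5 + *p* × (1 − *p*)/543.0), about 0.036. The two-sided rejection probability is Φ(*d*/SE − 1.96) + Φ(−*d*/SE − 1.96).

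- *d* = 0.027: *d*/SE = 0.75, giving 0.114 + 0.003, about 12%
- *d* = 0.050: *d*/SE = 1.39, giving about 28%
- *d* = 0.058: *d*/SE = 1.62, giving about 37%

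The nominal figure is 5%. With design effect 1.69 these figures change by less than one percentage point.

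**What a full 10-point artefact would take.** If a share *f* of the intervention arm is extra patients, the fall is *f* × (0.40 − *r*). Setting this to 0.10 gives *f* = 0.10/(0.40 − *r*): 25% if *r* = 0, 29% if *r* = 5%, 33% if *r* = 10%.

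**The case against.** A reader might infer that the article offers GP experience as its remedy for between-arm selection. It does not. The sentence stands under Generalisability and refers to variation among GPs, for which recording experience is relevant. The fair criticism is narrower: the article does not mention arm-related selection, and experience cannot quantify that form of inclusion bias.

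A reader might also infer that the analysis is fixed as unadjusted. That goes too far. GEE can carry covariates, and the full protocol or analysis plan, not shown, may name them. For the same reason the one-line statement on costs and QALYs, "Finally, costs and QALYs between the control and intervention groups will be compared", is a summary and not a commitment to an unadjusted comparison; I make no separate point of it. What stands is that the test the article does name leaves this bias untouched.

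Detection is not impossible either. The planned baseline comparison could reveal imbalance in recorded characteristics. It would not remove the bias, and it would not capture the GP's level of suspicion.

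Finally, the extra share, its referral rate and the design effect are all assumed, and the direction of selection is inferred. The text requires suspicion of ACS in both arms, which limits how far thresholds can drift. That GPs know the arm is also inferred, although no other reading fits a GP who runs the test.

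**Conclusion.** The concern holds in a limited form. The design allows case mix to differ by arm, the article recognises inclusion bias only as variation among GPs, and neither recording experience nor the described referral comparison deals with selection related to the arm.

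Under the stated assumptions the artefact is 2.7–5.8 points against a target of 10. It would raise the chance of a significant result under no effect from 5% to about 12% at the low end and about 28% for a 5-point artefact.

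The documents do not show that selection will occur, or that it could plausibly account for the whole planned effect: from a 40% base rate, that needs at least a quarter of the intervention arm to be extra patients. The point is that a moderate positive result could not be cleanly separated from a change in who was enrolled.

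**What to change.** 1. Make the primary referral analysis a GEE model adjusted for region (the randomisation stratum) and for pre-specified patient baseline variables recorded in both arms: age, sex, symptom duration, and cardiovascular history if recorded for all patients. Report a standardised risk difference, with the unadjusted result as a sensitivity analysis.
2. Report inclusions per practice and baseline risk by arm as a descriptive check on selection. Comparing 6-week ACS incidence is a poor substitute: with the article's 4–7% ACS, 20% extra patients without ACS and 448/896 patients, its power is only about 9–13% even ignoring clustering.
3. Limit the Generalisability sentence on GP experience to variation among GPs, and name arm-related selection as a limitation.
4. Make Table 1 agree with the text of Study population on suspicion of ACS.

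The cost is mainly wording, with no extra visit. Region, sex and symptom duration are already planned as subgroup variables. Whether cardiovascular history is recorded for everyone needs checking, because the article describes HEART scoring from the inclusion form only for patients with an ECG. Covariates must be fixed before any comparison by arm is seen. Adjustment reduces bias from measured risk only and cannot exclude residual selection through the GP's threshold of suspicion.

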### Patient involvement

During the design of the study, the writing of the protocol and the development of patient information materials, a participant of ‘Harteraad’, a patient advisory council for heart disease, was involved.

### Ethics and dissemination

The study will be conducted following the Declaration of Helsinki. The medical ethics committee Leiden-Den Haag-Delft has approved the protocol. Leiden University Medical Center is the sponsor of the study. Written informed consent will be obtained from all participating patients. The trial is registered in the Netherlands Trial Register (NTR) (https://www.trialregister.nl/), NL9525. Accepted on 20 June 2021. Due to the current process of merging the NTR into a new national registry, changes after protocol amendments cannot be made. Therefore, we registered the trial a second time on https://www.clinicaltrials.gov/, NCT05827237. A DSMB has been installed evaluating the safety of the study after 100, 500 and 1000 inclusions.

Results of the study will be shared with professional healthcare workers, participants and the general public. The primary outcomes of the study will be presented in one main paper in a scientific peer-reviewed journal. The cost-effectiveness and other secondary outcomes will be shared in separate papers. Findings will be shared at conferences through oral and poster presentations. At the end of the study, all participants will be informed of the study results through email or on paper. End results and interim updates will be shared on the website: www.pobhelp.nl. Participating GPs and other stakeholders will be kept up to date through a 3 monthly digital newsletter.
